# Transplantation of mesenchymal stem cells for prevention of acute myocardial infarction induced heart failure: study protocol of a phase III randomized clinical trial (Prevent-TAHA8)

**DOI:** 10.1186/s13063-022-06594-1

**Published:** 2022-08-04

**Keywords:** Regenerative medicine, Cell therapy, Myocardial infarction, Mesenchymal stem cells, Intracoronary injection, Acute myocardial infarction

## Abstract

**Background:**

Results from recent clinical trials on bone marrow mononuclear cell (BM-MNC) transplantation show that this intervention can help reduce the incidence of heart failure (HF) after acute myocardial infarction (AMI). However, no study has evaluated the effect of the transplantation of mesenchymal stem cells (MSCs) on a clinical endpoint such as HF.

**Methods:**

This single-blinded, randomized, multicenter trial aims to establish whether the intracoronary infusion of umbilical cord-derived Wharton’s jelly MSCs (WJ-MSCs) helps prevent HF development after AMI. The study will enroll 390 patients 3 to 7 days following AMI. Only patients aged below 65 years with impaired LV function (LVEF < 40%) will be included. They will be randomized (2:1 ratio) to either receive standard care or a single intracoronary infusion of 10^7^ WJ-MSCs. The primary outcome of this study is the assessment of HF development during long-term follow-up (3 years).

**Discussion:**

Data will be collected until Nov 2024. Thereafter, the analysis will be conducted. Results are expected to be ready by Dec 2024. We will prepare and submit the related manuscript following the CONSORT guidelines. This study will help determine whether or not the infusion of intracoronary WJ-MSCs in patients with AMI will reduce the incidence of AMI-induced HF.

**Trial registration:**

ClinicalTrials.gov NCT05043610, Registered on 14 September 2021 - retrospectively registered.

**Supplementary Information:**

The online version contains supplementary material available at 10.1186/s13063-022-06594-1.

## Introduction

Myocardial infarction (MI) represents a leading cause of mortality worldwide [1]. With a reduction in the rate of mortality due to MIs in recent decades, the incidence of heart failure (HF) has been on the rise [2]. This incidence ranges between 14 and 36% among those hospitalized due to an acute MI (AMI) [3]. HF exerts a considerable effect on healthcare systems in America, accounting for 6 million cases, 300,000 deaths, and roughly 40 billion USD worth of costs every year [4].

Despite the therapeutic efforts [5], post-MI HF still leads to a high rate of morbidities and mortalities [6, 7]. Although we have been successful in prolonging the life of HF patients and relieving symptoms, we are yet to regenerate the infarcted cardiac tissues. Hence, a gap exists in the literature as restoring the standard histological architecture of the heart should theoretically lead to improved outcomes for patients with MI-induced HF [6]. This may be possible using stem cell-based therapies [8].

### Cell-based therapy in cardiovascular disease

Toward the close of the 20th century, scientists signaled a new era in cardiovascular disease treatment through preclinical investigations in which skeletal myoblasts [9] and fetal cardiomyocytes [10] were transplanted into ischemic myocardium. Afterward, the intracardiac implantation of bone marrow (BM) cells was assessed in murine MI models [11, 12]. Human studies commenced following the turn of the century, with skeletal myoblasts being used in HF patients in 2001 [13] and BM cells being used for AMI patients in 2002 [14]. From then on, numerous investigations have aimed to amend the cardiovascular damage caused by diseases like MI and cardiomyopathy through the use of different cell-based therapies.

### Mesenchymal stem cells (MSCs)

The BM, heart, Wharton’s jelly, and adipose tissue are among the prime sources of MSCs [15, 16]. MSCs offer ease of isolation, ex vivo growth, in vitro proliferation, and immune-privileged properties, which is why their use in clinical trials is expanding rapidly [17]. According to the POSEIDON clinical trial on MSC transplantation, allogeneic MSCs are safe and as effective as autologous MSCs [18]. Notably, the TAC-HFT trial revealed the twofold effectiveness of MSCs relative to BM-derived mononuclear cells (BM-MNCs) [19]. Accordingly, MSCs appear to be an excellent candidate for cardiac regeneration trials. Few studies have used MSCs from Wharton’s jelly but the results from both clinical and preclinical studies for this resource are promising [20].

### Cell-based therapy in acute myocardial infarction (AMI)

To date, BM-MNCs have been used in the majority of research on cell-based therapy following AMI. The TIME trials established that the optimal time for cell implantation following AMI is within 3–7 days [21, 22]. Fisher et a., in a meta-analysis, proved that BM-MNCs augment the left ventricular ejection fraction (LVEF) following AMI by roughly 2.72%, yielding benefits both in terms of survival and function in AMI patients younger than 55 years of age with LVEF < 37% [23].

Trials involving the use of MSCs in patients following AMI have shown promising yet controversial results. Gao and coworkers conducted the largest clinical trial in this regard with 116 patients, demonstrating that umbilical cord-derived Wharton’s jelly MSCs (WJ-MSCs) led to an almost five percent improvement in the LVEF [24]. This figure was also confirmed in a meta-analysis for those who receive the cells in the first 10 days after AMI with an improvement of around at 5.74% [25]. These are in agreement with the findings of the TAC-HFT trial, which indicated the roughly twofold effectiveness of MSCs relative to BM-MNCs [19]. Also, a head-to-head comparison of BM-MNCs with MSCs in a meta-analysis showed similar findings (BM-MNC= 3.07%, vs MSCs = 5.65%) [26].

### BAMI trial

For over two decades, autologous cell-based treatments have been assessed in managing cardiovascular diseases through preclinical and clinical studies. However, phase III trials have been infrequent. Furthermore, the phase II trials have involved different methodologies in terms of the type of stem cells and the method and timing of delivery.

The BAMI trial was the first phase III trial conducted to clarify whether or not post-MI intracoronary transplantation of BM-MNCs would reduce all-cause mortality. Although the trial was designed to involve 3000 patients, it was stopped prematurely after the enrollment of 375 patients. Among them, 185 received BM-MNCs (intracoronary infusion) 2–8 days following primary percutaneous coronary intervention (PPCI), and the remaining 190 patients received optimal medical therapy as the control group. All-cause mortality after 2 years was 3.26% [*n*=6; 95% confidence interval (CI): 1.48–7.12%] with BM-MNCs compared to 3.82% (*n*=7; 95% CI: 1.84–7.84%) with optimal medical therapy. The main reason behind such results was that mortality was much lower than expected at the time of study design. At the start of the project in 2011, the literature held that following an AMI, the mortality rate from all causes after 2 years would be approximately 12% among those with an LVEF ≤ 45% post-reperfusion therapy [3]. However, the researchers noticed a 3.85% mortality rate while conducting the study, reflecting the evolution of primary angioplasty procedures in those years. Importantly, the investigators noticed that only five patients (2.7%, 95% CI: 1.0–5.9%) who received BM-MNCs were hospitalized due to HF during the 2 years of follow-up compared with 15 patients (8.1%, CI: 4.7–12.5%) who received optimal medical therapy (HR: 0.33, 95% CI: 0.12–0.88), representing the sole clinical benefit observed. BAMI showed us that taking mortality as an endpoint for stem cell therapy trials may be difficult to achieve as the primary endpoint in trials with medium sample sizes and the best clinical endpoint to assess is HF incidence. In a recent meta-analysis, it was again shown that injection of BM-MNCs was associated with a lower risk of composite end points of hospitalization for congestive heart failure (CHF), re-infarction, and cardiac-related mortality (91/1191 vs. 111/812, RR = 0.643, 95% CI = 0.489 to 0.845, *p* = 0.002). This effect was derived from both reduction of CHF (47/1220 vs. 62/841, RR = 0.568, 95% CI = 0.382 to 0.844, *p* = 0.005) and re-infarction rate (23/1159 vs. 30/775, RR = 0.583, 95% CI = 0.343 to 0.991, *p* = 0.046), but not cardiac-related mortality (28/1290 vs. 31/871, RR = 0.722, 95% CI = 0.436 to 1.197, *p* = 0.207) [27].

### Hypothesis generation

Since the efficacy of MSCs is higher than BM-MNCs after AMI in the improvement of LVEF, it would be probable that these cells may have a better clinical effect as well. However, no study has evaluated the impact of the transplantation of MSCs on a clinical endpoint such as HF.

## Materials and methods

### Study design

A randomized, multicenter, single-blinded phase III trial will be conducted to assess whether the intracoronary infusion of umbilical cord WJ-MSCs demonstrates a superior effect in reducing HF incidence following AMIs compared to standard treatment. The Ethics Committee of Shiraz University of Medical Sciences approved the study protocol (code: IR.SUMS.REC.1400.409). The trial is registered with https://clinicaltrial.gov under the code NCT05043610. This protocol was conceived following the Standard Protocol Items: Recommendations for Interventional Trials (SPIRIT) guidelines (Online supplement 1). Figure 1 depicts the SPIRIT flow diagram of the study.

**Fig. 1 Fig1:**
[figure not shown]
SPIRIT flow diagram of the study

### Sample size

Since the primary outcome of this study is to compare the incidence of HF and considering the one-year incidence rate of 1.3% and 4% in the BAMI trial [3], it is predicted that in a 3-year period follow-up of considered for the present study, the incidence rate of this indicator will be 3.9% and 12% in intervention and control groups respectively. According to the formula $$\boldsymbol{n}=\frac{\frac{\mathbf{1}+\boldsymbol{R}}{\boldsymbol{R}}\overline{\ \boldsymbol{P}}\Big(\mathbf{1}-\overline{\boldsymbol{P}\Big)}{\left({\boldsymbol{t}}_{\boldsymbol{\alpha}, \boldsymbol{\nu}}+{\boldsymbol{t}}_{\boldsymbol{\beta} \left(\mathbf{1}\right),\boldsymbol{\nu}}\right)}^{\mathbf{2}}}{{\left(\boldsymbol{\partial}\right)}^{\mathbf{2}}}$$, and the enrolment ratio of 2:1 in case and control groups, and considering the first type error of 5% and the power of 80%, the required sample size is approximately 220 people in control and 118 people in case group***s***, which makes a total of 328 people. To increase the accuracy of sampling and the possibility of using regression models, the sample size was increased to 390 people. The sample size is approximate and the above formula is summarized. In the above formula $$\overline{P}$$, the weighted average of the values in the two groups is used, and the *t* values are equal to the 0.8 and 0.975 percentiles of the standard normal distribution and equal to 1.96 and 84. The denominator of the fraction (∂) is the difference of two amounts. R is the ratio of two groups, which is 2 here.

### Study participants

A total of 390 patients with a history of an anterior ST-elevation MI (STEMI) treated successfully with PPCI 3–7 days earlier will be enrolled. Patients must be below 65 years old and must have severely impaired function of the left ventricle (LV), represented by an LVEF of < 40%. The participating hospitals will be the Al-Zahra Heart, Namazee, and Faghihi hospitals of Shiraz, Iran.

The inclusion criteria are as follows:Age (years): 18 to 65Either genderFirst MI in the preceding 3 to 7 daysPost-AMI LVEF < 40%Negative pregnancy test (for women of reproductive age)Written informed consent

The exclusion criteria are as follows:A history of any prior cardiac conditions (valvular, ischemic, or congenital disorders)Regional wall motion abnormalities outside the region of the infarctionLV dysfunction due to other etiologies like non-ischemic cardiomyopathy, anthracycline use, or ethanol abuse (> 6 oz./day regularly)Poor echocardiography windowActive infection, malignancy, or autoimmune disease

### Randomization and blinding

Randomization will be done via permuted block randomization through a web-based service (https://www.sealedenvelope.com/randomisation/simulation/). A block size of 6 will be considered. Two groups with a 2:1 proportion will be formed, where only one will receive an intracoronary infusion of WJ-MSCs besides the conventional therapy provided to both groups. Those who assess the study outcomes will remain unaware of the allocation (single-blind).

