### Intervention

This study will use cGMP-certified clinical-grade human WJ-MSCs (Cell Tech Pharmed Co. Ltd., Tehran, Iran). The cells will be transferred to the hospital on the same day as the infusion and are to be suspended in normal saline (0.9%). Each batch will be analyzed and certificated by a qualified individual, ensuring that the cells comply with the product specifications. Standard operational protocols will be followed during shipment and handling.

In the intervention group, all 130 patients will receive a single intracoronary infusion of 10^7^ WJ-MSCs alongside the conventional treatment that will be provided to the same number of patients in the control group. Patients in the intervention group will be taken to the cardiac catheterization lab, where the infusion of 10^7^ WJ-MSCs will be done through the intracoronary route. A bolus heparin dose (weight-based) is to be administered to patients with an activated clotting time below 200 seconds.

For catheterization, we will insert a therapeutic 6 Fr guiding catheter into the left coronary artery. Following the infusion of nitroglycerin (200 μg) through the catheter, we will assess the left anterior descending (LAD) artery and document the TIMI flow. A 0.014-inch soft-tipped guidewire wire will be inserted into the LAD at the distal edge of the stent. After passing through an over-the-wire balloon to the stented area, the balloon will be inflated until achieving occlusion. Following the removal of the guiding wire, we will connect an infusion syringe to the infusion catheter. WJ-MSCs will be infused at a rate of 2.5 ml/min and the total sample volume would be 7.5 cc. Low-pressure inflation (2–4 bar) will be performed to achieve occlusion with the balloon catheter, with complete coronary artery occlusion being ensured ahead of cell infusion through the use of dye. After the infusion of each third of the cells, we will pause the infusion, and TIMI coronary flow will be assessed with the contrast agent before the resumption of cell infusion. Once the cells are delivered across the three portions, we will place the coronary flow wire via the microinfusion catheter. No methods were used to increase adherence for this intervention as it was a one-off treatment with no need for continued adherence.

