The patients in both control and intervention groups will also receive standard Guideline directed medical therapy for acute myocardial infarction, consisting of Aspirin, ticagrelor, rosuvastatin, valsartan, and bisoprolol. Also based on the situation eplerenone and ICD insertion would be considered.

The original design of the study included a sham procedure for the control group but the local ethical committee refused that due to its invasive nature and obliged us to omit the sham procedure from the study protocol.

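### One fixed block size of 6, with allocations visible to treating staff, leaves up to 28.9% of assignments foreseeable; the share is about 3% to 11% if one list is shared and staff see only their own hospital's patients

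*Protocol article*

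**What the plan says.** Under Randomization and blinding, the protocol article states: "Randomization will be done via permuted block randomization through a web-based service". It adds "A block size of 6 will be considered" and "Two groups with a 2:1 proportion will be formed". No variation in block size is mentioned, and the section does not say whether the list is common to the three hospitals or separate for each. On blinding it says: "Those who assess the study outcomes will remain unaware of the allocation (single-blind").

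The Intervention section shows that the arm is visible at the bedside: "Patients in the intervention group will be taken to the cardiac catheterization lab". The ethics committee, the authors report, "obliged us to omit the sham procedure from the study protocol", so control patients have no matching procedure.

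Study participants gives the total of 390, and Intervention puts 130 patients in the cell-therapy arm. With 2:1 allocation, each block of 6 therefore holds 4 control and 2 intervention assignments.

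**The concern.** A web service hides the list itself. It does not stop staff who see past allocations from working out the end of a block of known, constant size. If the person deciding whether and when to enrol a patient knows the next arm, patients of higher or lower risk can be steered towards or away from it.

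The protocol leaves some room to act on such knowledge. Study participants allows enrolment on any of days 3 to 7 after infarction, requires LVEF below 40% and excludes a poor echocardiography window. Ethical considerations delays consent until the patient is clinically stable. Each is a legitimate judgement, but each can alter who enters or at which place in the sequence.

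Blinded outcome assessment does not protect against this, because the bias acts at enrolment. The planned number of heart failure events is small enough for a few steered patients to matter.

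**Working it through.** The article states no predictability figure, so there is none to reproduce.

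**Inputs.** Block size 6 and ratio 2:1 (Randomization and blinding); 390 patients (Study participants); 130 in the intervention arm (Intervention); expected heart failure incidence 3.9% and 12% (Sample size). 390/6 = 65 blocks.

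**Step 1: full sight of the list.** An assignment is certain when all remaining places in the block belong to one arm. The number of certain assignments is therefore the length of the final run of one arm. There are C(6,2) = 15 equally likely orders:

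| Block ends in exactly | Orders | Certain in each | Total |
|---|---|---|---|
| 1 control | 4 | 1 | 4 |
| 2 controls | 3 | 2 | 6 |
| 3 controls | 2 | 3 | 6 |
| 4 controls | 1 | 4 | 4 |
| 1 intervention | 4 | 1 | 4 |
| 2 interventions | 1 | 2 | 2 |
| All | 15 | | 26 |

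- Per block: 26/15 = 1.73 of 6, or 28.9%. Over 65 blocks: 112.7, about 113.
- Control: 20/15 × 65 = 86.7. Intervention: 6/15 × 65 = 26.
- At least the last two places are certain in (3 + 2 + 1 + 1)/15 = 47% of blocks.
- Guessing the likelier arm every time is right 74.4% of the time, against 66.7% for always guessing control.

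**Step 2: one shared list, own hospital only.** Suppose each patient on the list belongs to the observer's hospital with probability q, independently, and block boundaries are known. The 20/15 = 4/3 places per block that follow the second intervention assignment are certain only if both intervention patients were the hospital's own (probability q²). The 6/15 = 2/5 places that follow the fourth control are certain only if all four controls were its own (q⁴). So

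share certain = (4/3 × q² + 2/5 × q⁴) / 6

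- q = 1/3: (0.1481 + 0.0049)/6 = 2.6%
- q = 1/2: (0.3333 + 0.0250)/6 = 6.0%
- q = 2/3: (0.5926 + 0.0790)/6 = 11.2%
- q = 1: (1.3333 + 0.4000)/6 = 28.9%, which agrees with Step 1.

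**Step 3: varying block sizes.** These were simulated for 390 patients with sizes equally likely. The observer sees every earlier allocation and knows the set of sizes but not their order. The share certain is about 10% for sizes 3 and 6, 5% for 6 and 9, and 4% for 3, 6 and 9.

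**Step 4: how few patients matter.** Expected events are 130 × 0.039 = 5.1 and 260 × 0.12 = 31.2. As an illustration only, with Fisher's exact test standing in for the planned Cox regression, 5/130 against 31/260 gives p = 0.009. With two event patients moved between arms, 7/130 against 29/260 gives p = 0.066. Steering the other way could equally inflate a benefit.

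**The case against.** The strongest reply is that 28.9% depends on conditions the article does not establish. A reader might infer that staff see every allocation. The text shows only that they can see the arm of patients they treat. A reader might also infer that allocation is not stratified by hospital, but the article is silent on this. If that inference were right, a single list would serve three hospitals, and without sharing of allocation histories the relevant figures are 3% to 11%. Even those assume that staff know where blocks begin. This stands, and the 28.9% is a ceiling only.

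Most of the certain assignments are to control (about 87 of 113), already the likelier arm, and best-guess accuracy rises only from 67% to 74%. That also stands, and it limits the harm.

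Publication of the block size adds little. The article appeared on 4 August 2022, while Trial status gives recruitment from January 2021 to November 2022. About 19 of 23 planned months came before publication, and during them foreknowledge depended on staff knowing the protocol or inferring the size.

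The 3-to-7-day window limits how long a patient can be held back, and nothing says that those who enrol are those who infuse. These points shrink the opportunity without closing it.

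Finally, the roughly 4% left under mixed sizes is no lower than 2.6% on a shared list. That comparison mixes two assumptions: 4% is with full sight and 2.6% with partial sight. Like for like, varying the size lowers certainty under either list structure.

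**Conclusion.** The point holds as a cheap, avoidable weakness in a stated design choice. One constant block size is combined with treatment that staff can see. Certain assignments number up to 28.9% (about 113 of 390) if all earlier allocations on the list and the block boundaries are known. On a shared list seen through one hospital, they are about 3% to 11% at shares of one third to two thirds. Which range applies depends on the list type, which the article does not state. The 28.9% does not depend on which arm is the larger.

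A reader might go further and conclude that the primary comparison is biased. The documents do not support that. They give no sign that anyone used foreknowledge, and the two-patient illustration shows sensitivity, not an effect.

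**What to change.** For all remaining allocations, replace the fixed block of 6 with randomly varying 2:1 block sizes, for example 3, 6 and 9. Do not disclose the sizes to recruiting staff, and do not publish them until recruitment ends. Certain assignments then fall to about 4% even for someone who sees every earlier allocation and knows the set of sizes. What this removes is certainty; someone who tracks the whole list and knows the set can still guess somewhat better than always naming control, which is the reason to keep the set undisclosed.

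For allocations already made under the fixed block, use the stored list to mark each position as predictable or not. Then compare baseline risk between the two kinds of position within each arm, as a sensitivity check. At the ceiling this sets about 87 of 260 control and 26 of 130 intervention patients against the rest, so it can reveal gross steering but cannot rule out small amounts. If few allocations remain, this check carries most of the value.

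The cost is a new list set-up in the web service and a slight possible departure from exact 2:1 at the end of recruitment. The check needs only the list and baseline data.

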### Intervention

This study will use cGMP-certified clinical-grade human WJ-MSCs (Cell Tech Pharmed Co. Ltd., Tehran, Iran). The cells will be transferred to the hospital on the same day as the infusion and are to be suspended in normal saline (0.9%). Each batch will be analyzed and certificated by a qualified individual, ensuring that the cells comply with the product specifications. Standard operational protocols will be followed during shipment and handling.

In the intervention group, all 130 patients will receive a single intracoronary infusion of 10^7^ WJ-MSCs alongside the conventional treatment that will be provided to the same number of patients in the control group. Patients in the intervention group will be taken to the cardiac catheterization lab, where the infusion of 10^7^ WJ-MSCs will be done through the intracoronary route. A bolus heparin dose (weight-based) is to be administered to patients with an activated clotting time below 200 seconds.

For catheterization, we will insert a therapeutic 6 Fr guiding catheter into the left coronary artery. Following the infusion of nitroglycerin (200 μg) through the catheter, we will assess the left anterior descending (LAD) artery and document the TIMI flow. A 0.014-inch soft-tipped guidewire wire will be inserted into the LAD at the distal edge of the stent. After passing through an over-the-wire balloon to the stented area, the balloon will be inflated until achieving occlusion. Following the removal of the guiding wire, we will connect an infusion syringe to the infusion catheter. WJ-MSCs will be infused at a rate of 2.5 ml/min and the total sample volume would be 7.5 cc. Low-pressure inflation (2–4 bar) will be performed to achieve occlusion with the balloon catheter, with complete coronary artery occlusion being ensured ahead of cell infusion through the use of dye. After the infusion of each third of the cells, we will pause the infusion, and TIMI coronary flow will be assessed with the contrast agent before the resumption of cell infusion. Once the cells are delivered across the three portions, we will place the coronary flow wire via the microinfusion catheter. No methods were used to increase adherence for this intervention as it was a one-off treatment with no need for continued adherence.

The patients in both control and intervention groups will also receive standard Guideline directed medical therapy for acute myocardial infarction, consisting of Aspirin, ticagrelor, rosuvastatin, valsartan, and bisoprolol. Also based on the situation eplerenone and ICD insertion would be considered.

The original design of the study included a sham procedure for the control group but the local ethical committee refused that due to its invasive nature and obliged us to omit the sham procedure from the study protocol.

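### The Intervention section's equal arms contradict the 2:1 ratio and the total of 390, and the sample size calculation weights the ratio in the opposite direction to its own arm labels

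*Protocol article*

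**What the plan says.** All references are to the protocol article.

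- **Abstract, Methods:** "They will be randomized (2:1 ratio) to either receive standard care or a single intracoronary infusion". Standard care is named first, so in the order given this is 2 control to 1 cells.
- **Sample size, ratio:** "the enrolment ratio of 2:1 in case and control groups". In the order given this is 2 cases to 1 control.
- **Sample size, result:** the same sentence arrives at "approximately 220 people in control and 118 people in case" and continues "which makes a total of 328 people". Afterwards "the sample size was increased to 390 people".
- **Study participants:** "A total of 390 patients with a history of an anterior ST-elevation MI". The abstract and the Discussion also give 390.
- **Randomization and blinding:** "Two groups with a 2:1 proportion will be formed, where only one will receive an intracoronary infusion". The block size is 6; the larger arm is not named.
- **Intervention:** 130 patients receive cells, "alongside the conventional treatment that will be provided to the same number of patients in the control group".

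**The concern.** Two separate contradictions concern the arm sizes.

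The first is between sections. Equal arms of 130 make 260 patients at 1:1, which fits neither 2:1 nor 390.

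The second lies within the Sample size section. The ratio is worded with cases first, but the larger number goes to control. This would be only a matter of word order if the calculation did not depend on direction. It does, because the pooled rate in the formula is a weighted average of 3.9% and 12%, and doubling the weight of one arm or the other changes the required total considerably.

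At stake are the justification of the sample size, the 80% power on which the trial relies, and a clear statement of how many patients undergo the intracoronary procedure.

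**Working it through.** **Inputs (Sample size section).** Three-year HF incidence of 3.9% with cells and 12% in control, so the difference is d = 0.081; R = 2; two-sided 5% and 80% power, hence z = 1.96 and 0.84 (the second is printed as 84; I take it as 0.84, the 0.8 percentile that the section names). The formula is n = ((1+R)/R) × P̄(1−P̄) × (1.96+0.84)² / d², with P̄ the weighted average of the two rates. With R = 2, n is the smaller arm and 2n the larger.

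**Step 1: reproduce the stated size.**

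| P̄ weighting | P̄ | Smaller arm n | Larger arm 2n | Total |
|---|---|---|---|---|
| 2:1 towards cases | (2×0.039 + 0.12)/3 = 0.066 | 1.5 × 0.066 × 0.934 × 7.84 / 0.006561 = 110.5 | 221.0 | 331.5 |
| 2:1 towards controls | (0.039 + 2×0.12)/3 = 0.093 | 1.5 × 0.093 × 0.907 × 7.84 / 0.006561 = 151.2 | 302.4 | 453.6 |

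The stated 220 and 328 come out approximately (221 and 331) under the first weighting, in which the larger arm is the case arm. The article labels the 220 as control. With control as the larger arm, the same formula asks for about 454.

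**Step 2: check the sum.** 220 + 118 = 338, not 328, and 220/118 = 1.86, not 2. The 118 is not reproduced either; the formula gives 110.5.

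**Step 3: find the design that the whole text supports.** 390 − 130 = 260 controls, and 260:130 = 2:1. This agrees with the abstract's order, with the larger number being labelled control, with 130 infused, and with 390. It disagrees with the equal-number clause in the Intervention section and with the order of words in the Sample size ratio.

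**Step 4: power at 12% versus 3.9%.** Power = Φ((d − 1.96 × SE₀)/SE₁), with SE₀ from the pooled rate and SE₁ from the separate rates.

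- 260 control, 130 cells: SE₀ = √(0.093 × 0.907 × (1/130 + 1/260)) = 0.03120; SE₁ = √(0.039 × 0.961/130 + 0.12 × 0.88/260) = 0.02635; (0.081 − 0.06115)/0.02635 = 0.753; power 77.4%.
- 130 and 130: SE₀ = 0.03355; SE₁ = 0.03318; (0.081 − 0.06577)/0.03318 = 0.459; power 67.7%.
- 130 control, 260 cells: power 82.4%.

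Log-rank simulation over 3 years with constant hazards and no loss to follow-up gives 79 to 80% for 260 control and 130 cells, 68 to 70% for 130 and 130, and 84% for the reversed arms. The article's own formula, solved for power at 260 and 130, gives 0.081/0.03120 − 1.96 = 0.636, or 73.8%.

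**The case against.** The strongest defence is that the intended design can be inferred. The total is 390 wherever it is stated, and no section states 260 patients in all or 260 infused. The equal-number clause sits in a paragraph about delivering the treatment, and the ratio wording in the Sample size section is followed at once by named arm sizes. This largely stands, and it rules out three stronger readings that a reader might infer:

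- *The total sample size is undetermined.* The figure of 260 arises only by adding up one clause, against a consistent 390. The 68% power would apply only if the trial enrolled 260.
- *A trial with 260 infused patients is a live possibility.* The Intervention section's 130 rules it out, so the 82% describes no design that the article supports.
- *The randomization list is wrong.* Enrolment began in January 2021, so a list was already in use, and nothing in the article shows an error in it. That the Randomization section does not name the larger arm or the block composition is ordinary condensation in a journal article and not a fault in itself.

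A further defence is that the planned analysis is Cox regression, for which Schoenfeld's formula gives about 91% power at 260 and 130 (36.3 expected events, hazard ratio 0.311). This does not stand. The approximation is unreliable with so few events, an effect this large and unequal arms, and direct simulation of the log-rank test gives 79 to 80%.

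The defence also leaves Step 1 untouched. That the total reproduces only with the weighting reversed is more than loose word order.

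**Conclusion.** The point holds as an internal inconsistency with a consequence for the power statement. The equal-number clause contradicts 2:1 and 390. The Sample size section contradicts itself on direction, adds its arms to the wrong total, and obtains a figure near 328 from its formula only by weighting towards the arm that it labels as the smaller. For control as the larger arm, that formula needs about 454.

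For the design that the text as a whole supports, 260 control and 130 WJ-MSC, power is about 77% by the two-proportion method and 79 to 80% by log-rank simulation. The increase to 390 therefore does not clearly secure 80%. The shortfall is small. It comes from the calculation and not from any doubt about the total.

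These figures assume the article's rates of 3.9% and 12%, a two-sided 5% test and no loss to follow-up. The intended direction is inferred from the text and should be confirmed by the sponsor.

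**What to change.** 1. State one ratio with named arms and counts, and use it everywhere. If it is the design in use: 2:1 control to WJ-MSC, 260 control and 130 WJ-MSC, with 4 control and 2 WJ-MSC in each block of 6.
2. In the Intervention section, replace the equal-number clause with the control count (260 under that design).
3. In the Sample size section, put the arms in the order of the declared ratio and correct the figures 220, 118 and 328.
4. Redo the calculation with P̄ weighted to the declared ratio, and restate the power for 390 (about 77% by the two-proportion method at 260 and 130). Changing the wording alone would leave a claim of 80% beside a design that does not clearly deliver it. No additional enrolment is asked for.
5. Check the randomization list in use against the declared ratio.

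The cost is a text correction, one short recalculation and one check of the list.
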